## 5.5 Removal of Subjects from Study

Subjects can be taken off the study treatment and/or study at any time at their own request, or they may be withdrawn at the discretion of the investigator for safety, behavioral or administrative reasons. The reason(s) for discontinuation will be documented and may include:

- 
- 5.5.1 Subject voluntarily withdraws from treatment (follow-up permitted);
  - 5.5.2 Subject withdraws consent (termination of treatment and follow-up);
  - 5.5.3 Subject is unable to comply with protocol requirements;
  - 5.5.4 Subject demonstrates disease progression (unless continued treatment with study drug is deemed appropriate at the discretion of the investigator);
  - 5.5.5 Subject experiences toxicity that makes continuation in the protocol unsafe
  - 5.5.6 Treating physician judges continuation on the study would not be in the subject's best interest;
  - 5.5.7 Subject becomes pregnant (pregnancy to be reported along same timelines as a serious adverse event);
  - 5.5.8 Development of second malignancy (except for basal cell carcinoma or squamous cell carcinoma of the skin) that requires treatment, which would interfere with this study
  - 5.5.9 If a research subject cannot be located to document survival after a period of 2 years, the subject may be considered "lost to follow-up." All attempts to contact the subject during the two years must be documented and approved by the Data Monitoring Committee.

## 6.0 Data and Safety Monitoring Plan

### External Data and Safety Monitoring Board

The UTSW Simmons Cancer Center (SCC) Data Safety Monitoring Committee (DSMC) is the external review of trial-related documentation, which may include detailed assessment of subject records, regulatory and pharmacy review or may be more focused depending on the nature and reason for the audit. External reflects an independent reviewer within the CRO who is external to the DOT. DSMC audits are performed by the Quality Assurance and Education Coordinator (QAC) with the overall purpose of reviewing the conduct of a clinical trial to ensure quality results. The audit schedule prioritizes investigator-initiated institutional therapeutic trials and frequency is determined by the risk of the trial. Audits of other trial types are performed according to the risk level assigned to the study. The schedule is designed to ensure that every disease site will have trials audited at least annually.

The SCC DSMC is responsible for monitoring data quality and patient safety for all UTSW SCC clinical trials. As part of that responsibility, the DSMC reviews all local serious adverse events and unanticipated problems in real time as they are reported and reviews adverse events on a quarterly basis. The quality assurance activity for the Clinical Research Office provides for periodic auditing of clinical research documents to ensure data integrity and regulatory compliance.

A detailed description of the Data and Safety Monitoring Plan is available the Clinical Research Office Operations Manual.

The SCC DSMC meets quarterly and conducts annual comprehensive reviews of ongoing clinical trials, for which it serves as the DSMC of record. The Quality Assurance and Education Coordinator (QAC) works as part of the DSMC to conduct regular audits based on the level of risk. Audit findings are reviewed at the next available DSMC meeting. In this way, frequency of DSMC monitoring is dependent upon the level of risk. Risk level is determined by the DSMC Chairman and a number of factors such as the patient population to be studied; adequacy of the data management system; and procedures to ensure the safety of study subjects based on the associated risks of the study. Protocol-specific DSMC plans must be consistent with these

principles. The following examples can be used to begin developing DSMC plans for individual protocols.

- High risk examples include Phase I, II or III studies where the SCC is the DSMC; gene therapy or recombinant DNA studies; and studies in which the investigator holds the IND.
- Moderate risk examples include pilot studies and other Phase I, II or III studies where the SCC DSMC is not the DSMC of record and which involve a non-FDA approved drug.
- Low risk examples include Phase II or III studies involving FDA-approved drugs where the SCC DSMC is not the DSMC of record, or trials, which involve non-therapeutic interventions.
- Exempt examples include non-interventional studies, which are exempt from audit requirements outlined above.

#### Internal Data and Safety Monitoring Committee

The Radiation Oncology Clinical Research Office (CRO) reports serious adverse events (SAEs) to Radiation Oncology Data Safety Monitoring Committee (DSMC) monthly. These SAEs are also reported to the University of Texas Southwestern Medical Center (UTSW) IRB per IRB guidelines and SCC DSMC.

All clinical trials are reviewed on monthly basis for enrollment. These trials are assessed for safety on a continual basis throughout the life of the trial. For investigator-initiated trials, all SAEs are monitored – both local and at affiliated institutions.

## **8.0 Quality of Life**

### **8.1.1 EORTC QLQ C30 and H&N 35**

“European Organization for Research and Treatment of Cancer 30 (EORTC QLQ C-30)” is a 30 (10 minutes) question quality of life questionnaire that has been used in several current and prior European studies to assess quality of life in patients undergoing treatment for cancer. We will only collect this questionnaire in patients treated to lung, liver, and pancreatic sites based on the extensive European quality of life data which will serve as a general comparison for these disease sites. EORTC QLQ questionnaires are standard of care for RTOG trials in the Europe. The H&N 35 (10 minutes) is an additional add-on questionnaire exploring side effects commonly experienced by patients treated with radiation therapy and/or chemotherapy for head and neck cancers.

### 8.1.2 EQ-5D

The “EQ-5D” is a patient self-administrated questionnaire that takes approximately 5 minutes to complete (See appendix for form). The first part consists of 5 items covering 5 dimensions including: mobility, self care, usual activities, pain/discomfort, and anxiety/depression. Each dimension can be graded on 3 levels: 1-no problems, 2-moderate problems, and 3-extreme problems. Health states are defined by the combination of the leveled responses to the 5 dimensions, generating 243 health states to which unconsciousness and death are added.

The 5-item index score is transformed into a utility score between 0, “Worst health state,” and 1, “Best health state.” The index score or the cost-utility equation can be used in the quality adjusted survival analysis depending on the health state(s) of interest.

## 8.2 Cost effectiveness data collection:

Health care utilization data needed to assess costs will be obtained from treatment records. Additionally, in order to assess the treatment related indirect costs and patient out of pocket costs, a form will be administered during the last week of treatment or at the first available follow up visit after completion of radiation treatment (see Appendix VII).

- Hospitalizations: For hospitalizations with physician billing records, inpatient physician costs will be estimated by applying Medicare payment rates under the RBRVS-based Medicare Fee Schedule to billed procedures in the physician billing records.
- Treatment Cost: Direct costs of radiation treatment including consultation, simulation, treatment planning, and treatment delivery. Patient bills related to treatment will be obtained and estimated by total billed charges adjusted by facility-specific cost-to-charge ratio from Medicare cost reports as described above.
- Emergency Room visits: The date of ER visit and name of the facility, and whether the ER visit resulted in a hospital admission. ER costs will be estimated using Medicare average payment rates for facility and physician charges, using the merged MEDPAR and MBS data as described above.
- Physician and Clinic Visits: The date of the visit, the name of the physician or physician clinic, and the service provided (physician exam, lab test, physical therapy, etc.). Costs for physician and clinic visits will be calculated based on billing records obtained for such visits, using Medicare payment rates for procedures indicated in the clinic billing records.
- Medications: Prescription drugs used, including dosage strength and frequency of administration. Information about name, dose, and frequency of all prescription medications will be recorded. The medications used by the study patients will be assigned an NDC drug code. Unit costs for these drugs will be estimated as the “AWP” price published in the Red Book less 15%. Outpatient drug costs will be calculated by multiplying unit cost by the number of pills used per day times the length of time the patient received the medication. Note that costs of drugs administered through a clinic (e.g., reimbursed under Medicare Part B) are included under “clinic visit costs” and inpatient drug costs are included under “inpatient facility costs.”

## 9.0 QUALITY OF LIFE AND COST-EFFECTIVENESS

### 9.1 Health-Related Quality of Life (HRQOL) Analysis

The study design is to prospectively analyze the HRQOL among patients with early stage glottis cancer who are treated on this protocol. While hypofractionation is hypothesized to yield greater tumor cell kill, it may also increase the normal tissue toxicity, in which case there may be a decrease in HR-QOL. The primary normal tissue toxicities in patients receiving radiation

depends on the location of the treatment. Prior studies have demonstrated that the most sensitive and clinically meaningful method for accurately capturing the normal tissue toxicities is via patients reported outcomes (PROs), such as HRQOL.

In this non-randomized trial, we plan to assess the HR-QoL forms at specific time points to minimize patient burden: baseline (pretreatment), at the end of radiation, and at subsequent follow ups (See Appendix).

In addition, the EQ-5D will be used as well. EQ-5D is a standardized instrument for use as a measure of health outcome. Applicable to a wide range of health conditions and treatments, it provides a simple descriptive profile and a single index value for health status. The US version of the EQ-5D will be used, to enable mapping of general HR-QoL scores from EQ-5D scores into health state utility scores (ranging from 0 to 1) for the US population. These utility scores are needed for cost-utility analysis (estimates of costs per “quality adjusted” life-year gained).

HRQoL of patients with early stage glottis cancer is fortunately well documented but there exist wide variability in the forms used to assess HR-QoL and the majority of HR-QoL being reported for traditional fractionated radiotherapy, surgery, or laser techniques.

In a study from the Czech Republic evaluating the health-related quality of life of patients treated with either radiotherapy or endoscopic trans oral into laryngeal surgery, the authors concluded that was no difference between patients treated with the cordectomy and radiotherapy. They assessed health related quality of life using the EORTC-QLQ C30 and H&N 35 forms.

With the improved utilization of endoscopic laser surgery, a similar study assess the quality of life of patients undergoing laser surgery versus radiotherapy. Their health-related quality of life was assessed via EORTC-QLQ C30 and H&N 35 forms. The results of this study showed that both modalities achieved excellent quality of life in the treatment of early laryngeal tumors.

While numerous other studies use a wide range of questionnaires to assess health-related quality of life, we chose to use the EORTC-QLQ C30 and H&N 35 similar to the above-mentioned trials to aid in future comparisons.

All HR-QoL will be used for descriptive purposes only due the single arm phase I nature of this protocol.

Additionally, in order to calculate the indirect costs associated with hypofractionated radiation treatment, a single administration of a short economic questionnaire will take place at the end of radiation treatment or first available follow up or whichever occurs first. This questionnaire which has been adapted for administration in the United States has been used in economic assessments in rural Canadian cancer health service research.

## 9.2 Cost-Effectiveness Analysis (CEA)

For the primary CEA analysis, we will estimate cost accumulated within 1 years.

Since patients are enrolled into the study over time and some patients are still alive at the end of the study, their survival time and costs are censored. Due to the presence censoring, we cannot use a simple average of the patients’ total costs, a simple average of the patients’ costs for those with complete cost information, or a Kaplan-Meier estimator on censored costs, since these all produce biased estimators of the mean costs. Instead, we will use the inverse-probability weighting method to calculate average costs. The assumption used in this method is that censoring is independent of the survival time, or cost collection

process, which is often satisfied in well-conducted clinical trials. If the new treatment can both extend patients' survival time (or quality-adjusted survival time), and save costs at the same time, the new treatment will be preferred to the current standard treatment under any willingness to pay threshold.

However, if the new treatment extends survival time but costs more, cost-effectiveness analysis provides an estimate of the incremental cost of greater incremental effectiveness. For traditional cost-effectiveness analysis, treatment effectiveness is measured simply as survival time. The incremental cost-effectiveness ratio indicates the additional cost required to attain one additional year of survival. For cost-utility analysis, treatment effectiveness is measured as quality-adjusted survival time (which accounts for the impact of treatment on both mortality and morbidity, including any differences in adverse effects of treatment affecting HR-QoL). For cost-utility analysis, the incremental cost-effectiveness ratio indicates the additional cost required to attain one additional year of quality adjusted survival.

### **9.3 Projection Model and Sensitivity Analysis**

If the new treatment is implemented in usual practice, some of its potential benefits to patients may extend beyond the time horizon of the clinical trial. We will explore the potential to use results from the clinical trial based cost-effectiveness analysis, augmented with information from secondary sources, to develop a model to project costs and effectiveness beyond the time horizon included in the clinical trial. Any such model projections would be subjected to probabilistic sensitivity analysis, to assess the impact of parameter uncertainty on estimated cost effectiveness results. This is typically done via Markov Modeling with probabilistic sensitivity analysis.

Additionally, this Markov model will allow us to perform a value of information (VOI) analysis in order to assess from cost-effectiveness standpoint which variable(s) (i.e. voice quality, recurrence, salvage, HR-QoL) are most important to assess the future clinical trials.

### **9.4 Quality adjusted survival time:**

The quality-adjusted survival time estimates need to account for the presence of censoring. Due to the induced informative censoring problem, the ordinary survival method (e.g., Kaplan-Meier estimator) cannot be applied in this case. Accordingly, we will use the inverse-probability weighted method of Zhao and Tsiatis to carry out the survival time analysis. To estimate quality adjusted survival time, data from EQ-5D will first be translated into utility measures. These measures are obtained at discrete time points, so they will be interpolated into the time intervals between the visits. The quality-adjusted survival time is just an integration of the utility measures over a patient's survival time, or until the time limit similar as the cost calculation, whichever occurs earlier.

## **10.0 Statistical Considerations**

### **10.1 Primary endpoint**

The primary endpoint of this phase I clinical trial will be to either reach the minimum number of fractions that is tolerated for larynx irradiation or a dose of 42.5 Gy in 5 fractions whichever comes first. Patients will be treated in cohorts of 3-15. Toxicity will be graded using the National Cancer Institute (NCI) Common Toxicity Criteria for Adverse Events (CTCAE) version 4.0. A dose-limiting toxicity (DLT) is a grade 3 or greater toxicity definitely related to treatment in the following categories: laryngeal edema, voice, dyspnea, stridor, or cough. All reported DLTs will be verified by the study

chair, data monitoring committee, and as appropriate, independent review before final determination that a DLT has in fact occurred. The number of fractions will be reduced from 15, to 10 fractions, and then to 5 fractions (reduced by 5 fractions per step). The phase 1 portion of the study will be completed with either of the following events occur: 1) the MTD for a cohort is reached or 2) when the lowest number of fractions is treated and tolerated (42.5 Gy in 5 fractions).

## 10.2 Phase 1 waiting periods

Fraction reduction for this phase 1 clinical trial will not occur until sufficient waiting has occurred after a cohort has been treated. A period of 90 days must pass before further fraction reduction for the purpose of assessing toxicity. If 90 days have passed without a DLT at a dose level, the trial will be allowed to the next level, so long as either criteria for defining the MTD or criteria for further fraction reduction is not reached. If the maximum number of patients are enrolled to a given fraction level, yet criteria for follow-up is not reached in a representative sample of patients, further enrollment to the protocol will be suspended until adequate follow-up is reached. No action will be taken for Grade 1 or Grade 2 toxicities. If any 2 Grade 3 toxicities occur within a dose level likely or definitely related to radiation therapy, the trial will be terminated with reporting of DLT at that dose level. Any Grade 4 or Grade 5 toxicity found to be likely or definitely related to treatment will result in termination of the trial with reporting of DLT at that dose level.

Grade 3 toxicities likely or definitely related to protocol therapy will result in action in schema provided below:

[figure not shown]

For level -1, if a Grade 3 toxicity occurs, the trial will be terminated with reporting of DLT.

For level 0, if a Grade 3 toxicity occurs, a step de-escalation will occur to level -1. If no grade 3 toxicities are experienced at level 0, the trial will proceed to level 1.

---

For level 1, if there are no Grade 3 toxicities after initial enrollment of 7 patients, an additional 8 patients will be enrolled. If there is no grade 3 toxicity after enrollment of an additional 8 patients, the trial will proceed to level 2. If there is a 1 grade 3 toxicity in the additional 8 patients, the trial will proceed to level 2 at the discretion of the PI and DSMC.

For level 1, if there is 1 Grade 3 in the initial 7 patient cohort, an additional 8 patients will be enrolled. If there is an additional Grade 3 toxicity at this level, the trial will be terminated with reporting of DLT. If there are no further grade 3 toxicities in the additional 8 patients, proceeding to the next level will be done at discretion of the DSMC and PI.

For level 1, if there are 2 grade 3 toxicities in the initial 7 patient cohort, the trial will be terminated with reporting of DLT.

For level 2, if there are 0 grade 3 toxicities in the initial 7 patient cohort, the trial will enroll an additional 8 patients.

For level 2, if there is 1 grade 3 toxicity in the initial 7 patient cohort, the trial will enroll an additional 8 patients. If there is another grade 3 toxicity, the trial will be terminated with reporting of DLT.

For level 2, if there are 2 grade 3 toxicities in the initial 7 patient cohort, the trial will be terminated with reporting of DLT.

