### **2.2 Secondary Objectives**

- 2.2.2 To determine overall survival at 5 years.
- 2.2.3 To determine loco-regional control at 5 years as determined by physical exam, visualization of tumor by laryngoscopy, and CT-scan of the neck to determine if the primary tumor is controlled. A tissue biopsy or recurrent or persistent disease will be required to be considered a loco-regional failure.
- 2.2.4 To characterize functional voice quality of patients treated on this protocol.
- 2.2.5 To characterize the HR-QoL and PRO of patients treated on this protocol.
- 2.2.6 To determine cost-effectiveness of hypofractionated larynx irradiation.
- 2.2.7 To determine late toxicity as defined as treatment-related toxicity occurring  $\geq 18$  months from completion of radiation therapy.

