#### **4.13 Subject Replacement**

Three subjects within dose levels -1 and 0 must be observed for 90 days before accrual to the next higher dose level may begin. For level 1, 7 patients must be observed for 90 days before accrual to the next higher dose level. If a subject is withdrawn from the study prior to completing therapy without experiencing a dose limiting toxicity prior to withdrawal, an additional subject may be added to that dose level. Subjects missing 3 or more radiation treatments due to toxicity will not be replaced since these subjects will be considered to have experienced a dose limiting toxicity.

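### The protocol sets no observation time for declaring level 2 (42.5 Gy in 5 fractions) tolerated, and does not say whether a later related event overturns that call

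*Protocol*

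**What the plan says.** **Completion.** Section 10.1 ends phase 1 either at the MTD or "when the lowest number of fractions is treated and tolerated (42.5 Gy in 5 fractions"). No follow-up time is attached.

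**DLT definitions.** Section 10.1 says: "A dose-limiting toxicity (DLT) is a grade 3 or greater toxicity definitely related to treatment in the following categories", followed by five categories. Section 4.1 has a different definition (grade 4 or 5, three categories). Neither has a time limit.

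**The 90 days.** Section 10.2 says: "A period of 90 days must pass before further fraction reduction for the purpose of assessing toxicity", and then: "If 90 days have passed without a DLT at a dose level, the trial will be allowed to the next level". Section 4.13 asks for three subjects at levels -1 and 0, and adds: "For level 1, 7 patients must be observed for 90 days before accrual to the next higher dose level". It has no entry for level 2.

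**Termination.** Section 10.2 says: "If any 2 Grade 3 toxicities occur within a dose level likely or definitely related to radiation therapy, the trial will be terminated". Any related grade 4 or 5 event also terminates the trial. Both carry reporting of a DLT at that level, and neither has a time limit. For level 2 with one grade 3 event in the first 7 patients, 8 more are enrolled and: "If there is another grade 3 toxicity, the trial will be terminated with reporting of DLT".

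**Follow-up.** Visits run to year 5 (section 4.11), with DLT evaluation listed at follow-up (section 5.4). Late toxicity, from 18 months, is a secondary endpoint (sections 2.2.7 and 10.3).

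**The concern.** For levels 0 and 1, the 90 days works in substance as a DLT observation period: its stated purpose is to assess toxicity, and a DLT-free period lets the trial move on. But its only consequence is permission to open the next level. At level 2 there is nothing left to open, so the period has no force at the one level whose tolerability completes the primary endpoint by success, and which has the largest fraction size (8.5 Gy).

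The pass mark can be inferred from the termination rules: at most one related grade 3 event and no related grade 4-5 event in up to 15 patients. The time over which that count is taken cannot. Two teams following the text could report different primary results from the same 15 patients, one on the last treatment day or at day 90, the other at month 12 or 18.

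A smaller form of the gap affects level 1. Section 4.13 requires 90 days for only 7 of up to 15 patients, so level 2 could open with 8 level 1 patients not yet observed for that long.

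**Working it through.** **1. Where a time limit could come from.**

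| Place in protocol | What it times | Applies to level 2? |
|---|---|---|
| 4.1, DLT definition | nothing | no time given |
| 10.1, DLT definition | nothing | no time given |
| 10.1, completion | nothing | yes, but untimed |
| 4.13 | 90 days, before the next level opens | no; names levels -1, 0 and 1 |
| 10.2, waiting period | 90 days, before further fraction reduction | no; no further reduction exists |
| 10.2, general follow-up safeguard | suspends enrolment until follow-up is adequate (no number) | no effect once level 2 is full |
| 10.2, level 2 rules | count in 7, then 8 more | yes, but untimed |
| 10.2, terminations | nothing | yes, open-ended |

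No row gives a time at which level 2 may be called tolerated.

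**2. Design numbers.** The per-level numbers add up to the stated totals: minimum 3 + 7 + 7 = 17; maximum 3 + 15 + 15 + 15 = 48. Level 2 therefore has up to 15 patients, and fails on grade 3 events at two or more.

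**3. How far timing could change the result (illustration).** The documents give no toxicity rates for levels 1 or 2, so the rates are assumptions:

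- q = risk of a related grade 3 event by day 90 (month 3): 2% to 5%.
- R = further risk from month 3 to month 60: 5% to 10%, at constant hazard h = -ln(1 - R)/57 per month.
- Cumulative risk at month T: p(T) = 1 - (1 - q) exp(-h(T - 3)).
- Chance of failing: P(X ≥ 2), with X ~ Binomial(15, p(T)).

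| | q = 2%, R = 5% | q = 5%, R = 10% | Low case, q = R = 0.5% |
|---|---|---|---|
| Month 3 | 3.5% | 17.1% | 0.25% |
| Month 12 | 6.4% | 25.8% | 0.33% |
| Month 18 | 8.7% | 31.7% | 0.40% |

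The low case borrows the one severe toxicity in 200 patients (1/200 = 0.5%) that section 1.1 reports for 50-52.5 Gy in 16 fractions, a regimen close to levels -1 and 0, not level 2.

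**4. Chance of a reversal**, that is, at most one event at month 3 but two or more by month 18. With L = 1 - exp(-15h):

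P = P(0 early) × P(Bin(15, L) ≥ 2) + P(1 early) × P(Bin(14, L) ≥ 1)

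- q = 2%, R = 5%: L = 1.34%; 0.739 × 0.0168 + 0.226 × 0.172 = 5.1%.
- q = 5%, R = 10%: L = 2.73%; 0.463 × 0.0620 + 0.366 × 0.322 = 14.6%.
- Low case: L = 0.13%; 0.928 × 0.0002 + 0.070 × 0.0183 = 0.14%.

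Grade 4-5 events, where one is enough to fail, are not included.

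**The case against.** **The count is simply open-ended.** The terminations have no time limit, section 5.4 schedules DLT evaluation at follow-up, and section 4.11 runs to year 5. On this reading a related grade 3 event at month 9 counts whenever it occurs. This is fair as far as it goes, and it defeats a stronger reading that a reader might infer: that events between day 90 and month 18 fall outside every rule because they come before the late-toxicity endpoint begins. They are collected (section 5.1.8 covers acute and late events) and they remain under the termination rules. But an open-ended count does not say when level 2 can be declared tolerated, or whether the declaration survives a later event.

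**Ninety days is implied.** A reader may well assume it for level 2. The text ties it to further fraction reduction, and the untimed terminations point the other way. If 90 days is meant, one sentence settles it.

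**The consequences are limited.** This stands. No one is exposed to a further reduction because of an early level 2 call, no safety stop is lost, and data collection continues. A reader might infer a monitoring failure; the documents do not support that. What is exposed is the timing and meaning of the primary result.

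**The visit schedule might miss day 90.** Section 4.11 can be read as counting visits from the end of treatment, which puts the first quarterly visit near day 91. No finding is made on that point.

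**Unseen material.** The decision figure in 10.2 may carry a time. The point concerns the text, which sets out the rules level by level.

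**Conclusion.** The point holds for the text of the protocol. No observation time is given for calling level 2 tolerated; the 90-day rule does not reach it and, in section 4.13, covers only 7 of up to 15 level 1 patients. The open-ended terminations leave it unsettled whether a later related event overturns the call. This is more than detail that a statistical analysis plan could supply, because it governs conduct and the definition of the primary endpoint.

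The 5% to 15% chance of reversal is an illustration. It rests on assumed event rates, a constant hazard, independent patients and complete follow-up to month 18; the low case gives 0.1%. It shows that the gap matters if 8.5 Gy fractions are appreciably more toxic than the starting regimen, which is what the trial sets out to learn. It does not show that a reversal is likely, and the wording gap does not depend on it. The change should be made; confidence is moderate because the decision figure was not seen.

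**What to change.** 1. In 10.1, define the DLT window for every counted patient at every level as the first fraction to 90 days after the last fraction.
2. In 10.1, 10.2 and 4.13, require all treated patients at a level, including all level 2 patients, to complete the window before that level is called tolerated or the next level opens.
3. State the level 2 criterion directly: at most one related grade 3 event and no related grade 4-5 event within the window.
4. In 10.2, state that related events after day 90 still trigger the safety terminations while the trial is accruing or treating, but are reported by level as post-window toxicity beside the primary result and do not change the level's window-based DLT count. Without this sentence, a late termination would still report a DLT at a level already called tolerated.

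Cost: protocol wording only, with no extra patients or visits and no safety stop removed during accrual or treatment. The level 2 call waits about three months after the last level 2 treatment. Level 2 may also open up to three months later than if only 7 level 1 patients had to be observed.
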